## Abstract

Globally, lower respiratory infections (LRTIs) are one of the most common infectious diseases whichaffect majority of the population and as a result of inappropriate antibiotics practices lead to antibiotic resistance (AR). An individual randomized control trial will be conducted in the post-conflict areas of Swat, Pakistan, through a random sampling method. Patients aged > 18 years will be recruited from five community pharmacies and assigned to equally sized groups to receive either pharmacist-led education interventions or usual care with no intervention. A total of 400 (control = 200, study = 200) patients will be included, with prescriptions comprised of antibiotics for LRTIs. The outcomes measured in both groups will be a combination of treatment cure rate and adherence, which will be assessed using the Morisky Medication Adherence Scale and pill count. The trial comprises pharmacist-led educational interventions to improve treatment outcomes for patients with LRTIs. This study might establish the groundwork for pharmaceutical care of LRTIs patients with antibacterial therapy and the future delivery of a care strategy for the improvement of LRTIs treatment outcomes in post-conflict, remote areas of the third world and LMICs.

**Trial registration**: Chinese Clinical Trials Registry, identifier: ChiCTR2000040453, registered on 28 November 2020.

## 1. Introduction

Lower respiratory tract infections (LRTIs) are a type of acute sickness that lasts for 21 days or less and is characterized by the presence of at least one other lower respiratory tract symptom, in addition to the main symptom of cough (dyspnea, sputum, wheeze, or chest discomfort, and pain), with no other suitable explanation (e.g., sinusitis or asthma) [1]. Globally, LRTIs are one of the leading infectious diseases, the fifth overall cause of death, and the second most common cause of disability adjusted life years (DALYs), despite their being mainly preventable causes of mortality and morbidity [2]. Over the last ten years, the epidemiology of LRTIs has changed, with a rise in patients over the age of 70 [2]. LRTIs have no specific definitions besides the epidemiological perspective. LRTIs comprise bronchitis, acute exacerbations in chronic obstructive pulmonary disease (AECOPD), chronic obstructive pulmonary disease (COPD), pneumonia, community-acquired pneumonia (CAP), bronchiolitis, and influenza [2,3,4]. The LRTIs (2015) global burden of disease study noted that LRTIs were assessed to have caused 103.0 million DALYs and 2.74 million deaths [2]. However, pneumococcal pneumonia was found to be a cause of 55.4% of deaths in all age groups [2]. Worldwide studies from different regions, including North America [5], Latin America [6], Europe [7], and the Asia Pacific region [8], indicate the noteworthy clinical and economic load of the CAP disease. Antibiotic resistance was reported among CAP, with common pathogens, predominantly Streptococcus pneumoniae [5,8]. An African study reported that the pneumococcus remained susceptible to ampicillin/amoxicillin, which can still be used to treat the illness. The 1918 influenza pandemic killed over 50 million people, and while most influenza virus infections are self-limiting, there is still a significant number of severe infections that result in deaths, as influenza plays a considerably larger role in the etiology of CAP and AECOPD [9,10]. Moreover, patients with severe COPD and prone to acute exacerbations have more experience with antibiotics, and resistance may develop [11].

Nonetheless, antibiotics are still used for the treatment of LRTIs, resulting in the development of antimicrobial resistance [12,13]. Antimicrobials were originally regarded as lifesavers, with the best cure being antibiotics. However, incorrect antibiotic usage in the treatment of respiratory diseases might result in the emergence of resistance [14,15,16]. Antibiotics were misused in clinics because numerous isolates revealed high levels of antibiotic resistance; consequently, efficient antibiotic resistance surveillance is urgently needed to limit antibiotic abuse in China and Indonesia [17,18]. Treatment failure was more common in patients with RTIs in Pakistan because treatment outcomes are linked to antibiotic resistance [19].

Educational interventions could increase appropriate antibiotic prescription, dispensing, and/or use, which are commonly employed multimodal interventions [20,21,22]. Educational interventions at the community level reported a lower rate of antibiotic prescription, and enhanced knowledge of and attitudes towards antibiotic misuse [23]. Therefore, there has been no coverage of the topic, including educational interventions on patients recruited at community pharmacies, to improve adherence to antibiotic therapy in Pakistan. Hence, one of the barriers to care is the physical distance of rural communities from urban healthcare facilities. One of our baseline studies reported that the education of rural people is key to reducing the misuse of antibiotics [24].

The post-conflict areas (Swat) of Pakistan have witnessed extensive militancy since 2007. This has continued for many years, as the majority of the population of rural areas were displaced and migrated to the safest areas of the country [25]. During 2009, the people of Swat were asked to return after the area was cleared; however, the unremitting military presence and intermittent conflicts between security agencies and militants remain a social restiveness [26]. In the post-conflict areas of Swat, misuse of antibiotics occurs at a high frequency [24]. To address this gap, brief educational interventions will be delivered to the patients with LRTIs.

Therefore, this study aims to determine the adherence to prescribed antibiotics through educational interventions in post-conflict rural areas of Pakistan.

## 2. Materials and Methods

### 2.1. Objectives and Hypothesis

The main objective of the current trial is to test the adherence to LRTI treatment in the local/rural villages of Swat, Pakistan. The secondary objective is to assess the improvements and the success rate of the therapy. First, the quantitative part will be completed; then, a qualitative interview will be conducted.

The primary hypothesis is; the intervention group will gain knowledge of, and adhere to, the prescribed therapy for LRTIs at a higher rate than the control group at 2 and 7 weeks. The secondary hypothesis is as follows.

Post-assessment will be conducted in the second week and endpoint evaluation at the end of seventh week; participants who received the intervention are expected to report positive changes in terms of their adherence to the medication and a reduction in antibiotic storage. After the seventh week, those in the intervention group are more likely to stick to their prescribed medication. Following the quantitative phase of the research, a qualitative assessment will be conducted to determine its acceptability.

### 2.2. Study Design

This is a two-arm, single-blind, individual, randomized, controlled trial that will determine the effectiveness of pharmacist-led educational interventions for the patients who approached pharmacies with LRTI prescriptions. The present study will be conducted in a community-pharmacy setting in the rural region of Pakistan. The iRCT will be favored to reduce possible contamination between the two groups. The standard protocol items; recommendation for interventional trials (SPIRIT) used in the current trials are presented in Figure 1 and the checklist (Additional File S1).

### 2.3. Study Setting and Population

Swat, formally known as the ‘Yousufzai State of Swat’ (1849–1969), has a population of 2.3 million at present, and is one of the rural districts in the northern region of the Khyber Pakhtunkhwa, Pakistan. About 86% of the total population lives in rural areas [24,27]. Swat has witnessed extensive militancy/conflict Since 2007 [25]. In 2009, more than 2 million people in the valley became internally displaced persons (IDPs) across Pakistan during the vigorous conflict between the militants and the army [28]. In July 2009, these IDPs were asked to return, after the Government declared the area nonviolent, although the continuous military presence and the intermittent conflicts between security agencies and militants remained, creating social restlessness [26]. Infectious diseases remain high in number. The trial will be carried out in two (Khwazakhela and Janu) union councils in the Swat district, Khyber-Pakhtunkhwa Pakistan. The union council (UC) and neighborhood councils are the basic units in the new local government laws of administration in Pakistan with a population of 2000–10,000 per UC.

### 2.4. Data Collector’s Eligibility Criteria and Training

The data collector team will be comprised of healthcare workers (pharmacists, LHWs, and vaccinators). The trained pharmacists will select pharmacies (5 = control, 5 = interventional) to recruit participants, with their full consent (Additional File S2). Leaflets and materials related to the appropriate use of antibiotics will be provided to the participants at the pharmacies.

The data collector team will have the required qualifications, and the pharmacist must be registered with Pakistan Pharmacy Council (PPC) [29]. The pharmacist’s abilities are directly related to the quality of the study, which depends solely on the pharmacist’s competency. Consequently, the pharmacists involved in this study will have experience in previous patient-centered care services at community pharmacies or be engaged with population-based studies.

The pharmacists and other healthcare members must be trained for the counseling sessions with participants at community pharmacies. Effective training in communication skills will be held before the execution of the trials, and pseudo-patient training will be arranged to assess their counseling skills at community pharmacies. Finally, the principal investigator will approve the trained team for the trial.

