### 2.9. Randomization

Using a computer-generated random digit number, a biostatistician will construct a random allocation order that is independent of/blinded to participants and trial size. For every participant that is recruited, a sample 1:1 is used to allocate them into control and interventional groups. Finally, ten pharmacists will be randomized to the intervention and control arms 1:1 and the permuted method will be used. This will be accomplished by the study teams exchanging a list of pharmacists, each of whom has a unique number assigned to them. The status of allocation will be conveyed to the research team coordinators, who will notify individual pharmacists as soon as the participants’ agreement to trial participation is obtained by research teams.

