### 2.10. Concealment of Allocation

Before preceding to random allocation into either the control or intervention arm of the study, an informed consent/agreement ascertainment and eligibility will be obtained. The allocation will not be known to research assistants, participants, or trial representatives (pharmacists) until the point of randomization. Interventional households will only be known to research assistants. The participants will be introduced to the interventional arm facilitator individually, by mobile phone call. If the pharmacists and research teams are allocated to the control arm, they will continue to regularly contact the allocated UC.

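### Section 2.4 has trial pharmacists select pharmacies counted by arm, no section allocates pharmacies at random, and this conflicts with the declared individual randomisation

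*Protocol article*

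**What the plan says.** Section 2.4 (Data Collector's Eligibility Criteria and Training) states: "The trained pharmacists will select pharmacies (5 = control, 5 = interventional) to recruit participants". The selectors are trial staff, and the pharmacies are counted by arm.

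Other sections place the allocation elsewhere:

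- **Patient.** Section 2.2: "This is a two-arm, single-blind, individual, randomized, controlled trial". Section 2.9: "For every participant that is recruited, a sample 1:1 is used to allocate them into control and interventional groups". Abstract: "Patients aged > 18 years will be recruited from five community pharmacies and assigned to equally sized groups".
- **Pharmacist.** Section 2.9: "ten pharmacists will be randomized to the intervention and control arms 1:1 and the permuted method will be used", and on the method, "This will be accomplished by the study teams exchanging a list of pharmacists, each of whom has a unique number assigned to them". Section 2.10 also treats staff as belonging to an arm: "If the pharmacists and research teams are allocated to the control arm, they will continue to regularly contact the allocated UC".

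The biostatistician's task is given in 2.9: "a biostatistician will construct a random allocation order that is independent of/blinded to participants and trial size". Drawing or allocating pharmacies is not mentioned there or anywhere else in the article.

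**The concern.** Pharmacies plausibly differ in clientele, nearby prescribers and counselling habits, and any of these can affect knowledge, beliefs and adherence. If a pharmacy serves one arm only and staff decide which pharmacies go to which arm, the arms can differ at site level before any patient is approached. Recruiting more patients per pharmacy does not shrink such a difference, and it cannot be undone after recruitment. Section 2.7 sets no quota per pharmacy, so a few chosen sites could dominate an arm. The mixed model in 2.17 names baseline BMQ and PAS-QA as covariates and subjects as the random effect; it names no pharmacy term.

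**Working it through.** **Reading the sections together.** The article gives no figure for between-site differences, so the main check is whether its statements fit one another.

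1. *Patients are the unit (Abstract, 2.2, 2.9).* Each pharmacy can then supply both arms, and the choice of sites affects generalisability, not the comparison. But the arm counts in 2.4 would then have no meaning.
2. *Pharmacists are the unit (2.9, 2.10).* Ten pharmacists drawn 1:1 gives five and five, the same split as in 2.4. If each is tied to one pharmacy before the draw, the sites are randomised too. If a pharmacist is drawn first and a site is chosen afterwards, the arm is random but the site is not. The article gives neither the tie nor the order.
3. *Pharmacies are the unit (2.4 read literally).* Staff select five for each arm and no random step is described.

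Readings 1 and 2 protect the comparison only with a condition that 2.4 contradicts or that is not stated. The number of pharmacies is five in the Abstract and ten in 2.4.

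**Illustration of size.** Inputs from the article: 200 per arm and 20% attrition (2.7), so 200 × 0.8 = 160 completers per arm; five pharmacies per arm (2.4), so 160 / 5 = 32 completers per pharmacy if recruitment is equal. Assumed, not in the article: 50% adherence, ICC 0.01, 0.03 or 0.05, and a correlation of 0.3 between staff choice and site quality.

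- Between-pharmacy SD on the proportion scale = √(ICC × 0.25).
- Best five minus worst five of ten standard-normal site effects averages 1.477 SD (simulation). This is full sorting, an upper bound.
- Partial sorting = 0.3 × full sorting.
- Half-width of the 95% interval for the arm difference, ignoring clustering = 1.96 × √(2 × 0.25 / 160) = 0.110.
- Design effect = 1 + (32 − 1) × ICC; clustered half-width = 0.110 × √(design effect).

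| ICC | Site SD | Full sorting (points) | Correlation 0.3 (points) | Design effect | Clustered half-width (points) |
|---|---|---|---|---|---|
| 0.01 | 0.050 | 7.4 | 2.2 | 1.31 | 12.5 |
| 0.03 | 0.087 | 12.8 | 3.8 | 1.93 | 15.2 |
| 0.05 | 0.112 | 16.5 | 5.0 | 2.55 | 17.5 |

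A random draw of sites has an expected difference of 0. The 11-point half-width is the right scale only without clustering; if pharmacies carry the arm, the last column applies.

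**The case against.** The strongest reply is that 2.4 gives only a count per arm and does not say that the pharmacists decide which pharmacy gets which arm. Staff may pick ten sites, and the 1:1 draw of ten pharmacists in 2.9 may then split them five and five. With one pharmacist per pharmacy, the link from site to arm is random. If patients are randomised within each pharmacy, as the Abstract and Sections 2.2 and 2.9 indicate, site choice cannot bias the comparison at all. Both arguments stand as possible readings. The article confirms neither, and the second leaves the arm counts in 2.4 unexplained.

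A reader might also infer that pharmacists learn their arm and then choose a pharmacy to suit it. The documents do not support this. Section 2.10 says allocation is unknown to pharmacists until randomisation, 2.9 times their notification to the participant's agreement, and Table 3 lists duty pharmacists as not aware at allocation.

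The illustration is open to criticism as well. It rests on assumed values, and it concerns adherence, which 2.14.2 makes a secondary outcome; for the BMQ and PAS-QA the planned model adjusts for baseline. The absence of a stated adjustment for adherence is no fault here, because 2.17 defers detail to statistical plans that are not shown.

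**Conclusion.** The defect is firm as an inconsistency: the protocol names patient, pharmacist and arm-specific pharmacy as the unit of allocation, gives five or ten pharmacies, and never states how a pharmacy reaches an arm. The bias is conditional. It arises if 2.4 is followed as written with arm-specific sites and no prior tie between pharmacist and pharmacy. It would be wrong to conclude that staff are known to assign the arms, or that randomising patients or pharmacists cannot protect the comparison; either could, under conditions the article does not state.

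The size is unknown. On the assumptions above it is about 2 to 5 points under partial sorting and at most 7 to 17 points under full sorting, against a half-width of 11 points without clustering or 12.5 to 17.5 with it. The wording should be settled before recruitment.

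**What to change.** **To match the declared individual design (the simpler route).** Delete the bracketed arm counts from 2.4. State that the participating pharmacies are listed before recruitment, that every listed pharmacy recruits to both arms, and that each patient's arm comes from the biostatistician's list in 2.9. Bring the pharmacist draw in 2.9 and the control-arm staff sentence in 2.10 into line with this, and reconcile five with ten pharmacies. This is a wording amendment with no extra patients or procedures. Staff lose the freedom to match sites to arms for convenience, and each pharmacy must handle both arms.

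**If pharmacies or pharmacists are meant to carry the arm.** Fix and record the list of pharmacies, with one pharmacist tied to each, before any arm is known. Have the biostatistician draw all the arms in one step, and stop describing the trial as individually randomised. The draw itself costs little, but the trial becomes cluster-randomised with ten clusters. The power and precision in 2.7 must then be restated allowing for clustering, and at the ICCs assumed here 400 patients would give less than an individually randomised trial of that size.

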### 2.5. Intervention Group

We have designed educational interventions and a brief, telephone-based intervention strategy will be developed for the EATSA based on WHO/CDC evidence-based guidelines for antibiotics adherence. Before its implementation, a period of formative and contextual work will be adopted, especially training in the intervention materials, to the study population in rural areas of Pakistan.

#### 2.5.1. Pharmacists Lead Educational Interventions at Community Pharmacies

Firstly, at the community pharmacy, a trained pharmacist and team will provide written information to the intervention group participants about the use of antibiotics and adherence to the prescribed antibiotics therapy for LRTIs, and discourage the storage of antibiotics at home. An educational leaflet will be designed, containing information based on ‘Get Smart: Know when Antibiotics work’ by CDC [30]. The written-material brochures adopted from the WHO/CDC awareness groups will be translated into the national and local language (Urdu/Pushto) for better understanding with the help of experts. At present, in Pakistan, patients are still deprived of proper counseling and instructions, and labels for prescribed medications are only provided as handwritten signs and descriptions. Therefore, the top section of the leaflet will have space reserved for directions on antibiotics’ use. The bottom section of the leaflet will contain information related to the importance of antibiotics’ adherence and forgetfulness, appropriate disposal, counseling on storage, the importance of not sharing the antibiotic with other people, and the risk of ABR. The leaflet’s content will be validated by two clinical pharmacists and consultant physicians specializing in infectious diseases (Figure 1). Based on the above-mentioned strategy, a full intervention will be provided to the individual LRTIs patients at time zero, and then followed to the start of the second week.

#### 2.5.2. Telephone-Based Follow-Up

After the educational interventions at the community pharmacies, a follow-up will be continued up until the 7th week. The first telephone call will be made at the start of the second week and the therapy success will measure the rate of adherence to the prescribed antibiotics. Then, a follow-up with a brief educational strategy will continue throughout the study period, and a 3rd, 4th, 5th, and 6th call will be made to enhance the participants’ knowledge related to proper antibiotics use. The 7th week of the trial will be the assessment week and will measure the overall knowledge as a primary and secondary outcome.

### 2.6. Boost Usual Care (BUC)

Participants in the intervention and control (arms) groups will continue to receive pre-planned, routine telephone calls on an individual basis and the care would be considered enhancement care. The primary care, the antibiotics therapy, will not involve any placebo, and the focus will adhere to the prescribed treatment. The usual care will consist of: (i) primary healthcare provider, pharmacists and assistants trained in interaction with and supervision of treatments with antibiotics; (ii) providing feedback results to all participants about their assessment; (iii) information will be provided about the options for appropriate care and treatment through the nearest tehsil headquarter hospital (THQ) or tertiary care facility.

Both arms are equally free to BUC through their routine health providers. Finally, on the 7th week, the strength of the services will be measured. The evaluation will be carried out and reported in a timely manner.

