### 2.11. Data Collection

At first, data from patients’ medical records reporting LRTIs (medical notes will be checked for the diagnosis) would be collected by trained pharmacists at community pharmacies, and the pharmacist team will remain blinded to the outcomes. A complete booklet of educational written information will be provided to participants in each interventional arm. The booklet will include materials that are relevant to antibiotic use, such as graphical leaflets, antibiotic dosing regimens kept on sticky notes, adherence, and prevention of antibiotic storage in the home. Following this textual counseling, oral/verbal counseling will be delivered in the patient’s usual area of counseling at a pharmacy. The patient’s information will be transferred to pre-determined data collection forms and stored securely. For the follow-up phase, patients’ valid mobile phone numbers will be collected and retained for future contact and follow-up. The trial team members will contact the participants through their mobile phones in both union councils. After one week, patients will be asked to exhibit their prescribed antibiotics, and the first therapy outcomes will be checked at the beginning of the second week. Finally, in the final session of the trial, a qualitative interview will be scheduled for the 7th week of the study. To keep data quality high, data collection should be current and dependable. As a result, at least three meetings will be held for the field assistance members (pharmacists) to keep the records up to date. The lead investigator will collect all data once a week, as in Table 2.

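### The protocol contradicts itself on what the control arm receives: no intervention in the abstract, enhanced care with calls and result feedback in section 2.6, and leaflets not tied to an arm in section 2.4

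*Protocol article*

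**What the plan says.** **Label of the comparator.** In the abstract, patients are "assigned to equally sized groups to receive either pharmacist-led education interventions or usual care with no intervention".

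**Content of the comparator.** Section 2.6 (Boost Usual Care) states: "Participants in the intervention and control (arms) groups will continue to receive pre-planned, routine telephone calls on an individual basis". It adds that "the care would be considered enhancement care". The listed components are:
- staff, described as "pharmacists and assistants trained in interaction with and supervision of treatments with antibiotics";
- feedback, in item "ii) providing feedback results to all participants about their assessment";
- information on where to obtain further care.

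The section also says: "Both arms are equally free to BUC through their routine health providers".

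**Written material.** Section 2.4 mentions five control and five interventional pharmacies, then says: "Leaflets and materials related to the appropriate use of antibiotics will be provided to the participants at the pharmacies". Section 2.5.1 gives the written information to the intervention group. Section 2.11 says: "A complete booklet of educational written information will be provided to participants in each interventional arm".

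**Outcome and timing.** Section 2.14.1 measures the primary outcome with the BMQ (beliefs about medicines) and the PAS-QA (antibiotic knowledge and resistance). Section 2.1 places assessments at weeks 2 and 7. Section 2.5.2, under the intervention group, describes later calls meant to raise knowledge of antibiotic use.

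**The concern.** A trial result is only interpretable against a known comparator. Here the abstract and section 2.6 describe different ones, and on leaflets sections 2.4, 2.5.1 and 2.11 do not agree. Two things are at stake.

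First, the conclusion. An effect reported against no intervention would describe a comparison that the trial, run as section 2.6 describes, did not make.

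Second, the contrast itself. The primary outcome is knowledge and belief about antibiotics. Leaflets about antibiotics, or a return of results on knowledge and belief questionnaires, could move that outcome in controls. Section 2.2 justifies the design by the wish to limit contamination between groups, so the protocol itself treats this as a threat.

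**Working it through.** The question is mainly one of text, so the statements are set side by side.

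| Element | Statement covering controls, or naming no arm | Statement limiting it or pointing the other way |
|---|---|---|
| Any intervention | Section 2.6: calls, trained staff, feedback for both arms | Abstract: none |
| Leaflets and materials | Section 2.4: participants at the pharmacies, no arm named | Sections 2.5.1 and 2.11: intervention arm |
| Telephone calls | Section 2.6: scheduled calls in both arms, content not described | Section 2.5.2: educational calls, under the intervention group |
| Feedback of results | Section 2.6(ii): all participants; which assessment and when are not stated | None |

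**Step 1: is the care in section 2.6 ordinary local care?** By the protocol's own account it is more than that. Section 2.5.1 says that patients in Pakistan still lack adequate counselling and receive only handwritten labelling. Trained supervision, scheduled calls and feedback go beyond this, and section 2.6 itself uses the word enhancement. The abstract and section 2.6 therefore cannot both describe the control arm.

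**Step 2: do controls get leaflets?** The text does not settle it. Read literally, section 2.4 covers participants at all ten pharmacies. Sections 2.5.1 and 2.11 point to the intervention arm. This is a conflict to reconcile.

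**Step 3: could feedback affect the primary outcome?** It could, if the assessment in section 2.6(ii) includes the BMQ or PAS-QA and results are returned between baseline or week 2 and week 7. The wording allows this and does not require it.

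**Step 4: can the loss be sized?** Not from the documents. Section 2.7 states 80% power, alpha 5%, 20% attrition and 400 patients, but no effect size, SD or rates, so the power-based figure of 400 cannot be reproduced. The precision statement in the same section does not give it either: with an assumed proportion of 0.5, n = 1.96² × 0.25 / 0.05² = 385 after rounding up, and 385 / 0.8 = 482 with attrition.

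An illustration is possible only under assumptions: two-sided alpha, 200 × 0.8 = 160 evaluable per arm, and a planned effect equal to the smallest one detectable with 80% power, d = (1.960 + 0.842) × √(2/160) = 0.313 SD. If a fraction f of the contrast is lost, power = Φ(d(1 − f)√80 − 1.960):

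| Assumed f | Power |
|---|---|
| 0 | 80% |
| 10% | 71% |
| 20% | 61% |
| 30% | 50% |

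Both d and f are assumed. Section 2.7 also ties the sample size to adherence, while the mechanism in Step 3 concerns knowledge and beliefs. The table shows how power responds to lost contrast in general; it is not an estimate for this trial.

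**The case against.** The strongest defence is that section 2.6 openly describes an enhanced background that both arms receive. Education on top of that background, against the background alone, is a legitimate add-on comparison. Its effect estimate is not biased merely because background care is good, and equal contact can balance attention and follow-up. In the abstract, the phrase about no intervention follows directly on the educational intervention and can be read as no educational intervention. All of this stands as far as it goes, but it does not make the abstract's label accurate for an arm that receives what section 2.6 lists.

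A reader might infer three stronger things that the documents do not support:
- *That controls will receive the leaflets.* Only the unrestricted sentence in section 2.4 points that way, and it sits in a section on data collectors. Sections 2.5.1 and 2.11 point the other way.
- *That controls are coached on the outcome questionnaires.* Section 2.6(ii) does not say which assessment is meant or when results are returned. The section goes on to measurement in week 7 and timely reporting, so feedback after week 7 fits the text equally well. Nor does any passage say that control calls carry education.
- *That the effect is biased towards zero.* For the add-on contrast this would need leaflets, feedback or calls that actually teach controls. A loss of planned power could also arise if the planned effect had assumed an unenhanced control. The documents show none of these.

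**Conclusion.** The contradiction is real and rests on the text alone: the abstract's comparator is not the one in section 2.6, and section 2.4 conflicts with sections 2.5.1 and 2.11 on written material. The add-on contrast is valid, provided it is named as such and kept clean.

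Dilution is conditional. It would occur if section 2.4 were followed literally in control pharmacies, or if BMQ or PAS-QA results reached controls before week 7. Its size cannot be computed from the documents, and the power figures above are an illustration only. The point still deserves correction before recruitment, because the present wording permits both routes and would lead to a conclusion against a comparator that the trial did not use.

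**What to change.** 1. In the abstract and in the conclusions, name the comparator *enhanced usual care*.
2. In section 2.4, limit the educational leaflets and materials to intervention participants, in line with sections 2.5.1 and 2.11.
3. In section 2.6(ii), state that BMQ and PAS-QA results are returned in both arms only after the week-7 assessment. Leave any feedback that is part of clinical care unchanged.
4. In section 2.5.2, or in section 2.6, state that the educational calls are for the intervention arm only.

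The cost is a few sentences and matching instructions to field staff. The one downside is that participants receive their questionnaire results a few weeks later. The sample size does not have to change on account of this point.
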